# Personalised selection of medication for newly diagnosed adult epilepsy: study protocol of a first-in-class, double-blind, randomised controlled trial

**DOI:** 10.1136/bmjopen-2024-086607

**Published:** 2025-04-05

**Keywords:** Artificial Intelligence, Machine Learning, Epilepsy, Clinical Trial

## Abstract

**Introduction:**

Selection of antiseizure medications (ASMs) for newly diagnosed epilepsy remains largely a trial-and-error process. We have developed a machine learning (ML) model using retrospective data collected from five international cohorts that predicts response to different ASMs as the initial treatment for individual adults with new-onset epilepsy. This study aims to prospectively evaluate this model in Australia using a randomised controlled trial design.

**Methods and analysis:**

At least 234 adult patients with newly diagnosed epilepsy will be recruited from 14 centres in Australia. Patients will be randomised 1:1 to the ML group or usual care group. The ML group will receive the ASM recommended by the model unless it is considered contraindicated by the neurologist. The usual care group will receive the ASM selected by the neurologist alone. Both the patient and neurologists conducting the follow-up will be blinded to the group assignment. Both groups will be followed up for 52 weeks to assess treatment outcomes. Additional information on adverse events, quality of life, mood and use of healthcare services and productivity will be collected using validated questionnaires. Acceptability of the model will also be assessed.

The primary outcome will be the proportion of participants who achieve seizure-freedom (defined as no seizures during the 12-month follow-up period) while taking the initially prescribed ASM. Secondary outcomes include time to treatment failure, time to first seizure after randomisation, changes in mood assessment score and quality of life score, direct healthcare costs, and loss of productivity during the treatment period.

This trial will provide class I evidence for the effectiveness of a ML model as a decision support tool for neurologists to select the first ASM for adults with newly diagnosed epilepsy.

**Ethics and dissemination:**

This study is approved by the Alfred Health Human Research Ethics Committee (Project 130/23). Findings will be presented in academic conferences and submitted to peer-reviewed journals for publication.

**Trial registration number:**

ACTRN12623000209695.

STRENGTHS AND LIMITATIONS OF THIS STUDYMultisite, prospective, double-blind, randomised, controlled trial of a machine learning model for antiseizure medication (ASM) selection for newly diagnosed epilepsy.Besides measuring the cost-effectiveness of applying the machine learning model, the acceptance of machine learning-assisted clinical decision support will be explored among different stakeholders, including both patients and neurologists.The trial confines the choice of drug to seven commonly prescribed ASMs, limiting the flexibility of neurologists who may have prescription preference outside the repertoire.The inclusion criteria of aged 18–67 specifically exclude the older adult epilepsy cohort who have a high prevalence of epilepsy along with distinct health and social needs that could be alleviated by optimised initial ASM selection.The model is used both on patients with generalised epilepsy or focal epilepsy, planned subgroup analysis is limited to these two epilepsy types and does not include more specific aetiologies.

## Introduction

 Epilepsy is a common chronic, serious neurological disorder that affects all age groups and ethnicities worldwide. Over 50 million people are living with epilepsy, accounting for 13 million disability-adjusted life-years.^1^ Antiseizure medications (ASMs) are the mainstay of epilepsy therapy, with the primary goal of achieving the best possible quality of life by maximising seizure control and minimising adverse effects.^2 3^ For a newly diagnosed patient, it is recommended to start an ASM as monotherapy. In the current treatment paradigm, a clinician selects an ASM according to the patient’s characteristics including demographics, epilepsy type/syndrome, comorbidities, while also considering the ASM efficacy spectrum and tolerability/safety profile. There are more than 20 ASMs available; among those approved for use as monotherapy, none has shown overwhelming superiority in terms of efficacy and tolerability.^4^ Choosing the ideal ASM for an individual can be a subjective and even biased process. There is no reliable biomarker to predict which ASM will be the most effective for an individual patient. As a result, people with epilepsy can undergo multiple trials of various medication regimens before attaining seizure freedom.^5^ The consequence can be years of poor quality of life,^6^ productivity loss^7^ and even increased risk of mortality.^8^

Failure of the first ASM is the strongest predictor of long-term drug resistance and poor health outcomes.^9 10^ Choosing the first ASM is arguably the most important decision to be made in the management of newly diagnosed epilepsy from the perspectives of both clinical outcome and the patient’s preference. Hence, it would be of great clinical value if the most effective one could be prescribed at the outset instead of going through the current trial-and-error process.

Machine learning (ML) is a subfield of artificial intelligence (AI). It has the advantages in recognising hidden patterns in input variables and making meaningful predictions. Our group has recently developed a deep learning model, a type of ML model with multiple layers, that used 16 structured clinical variables to predict the effectiveness of ASMs in adults with newly diagnosed epilepsy.^11^ The model was trained and tested on five independent cohorts from four countries (UK, Malaysia, Australia, and China) totalling 1798 patients. It was trained to predict and rank the likelihood of treatment success (seizure freedom at 12 months without intolerable adverse effects) of each of the seven predefined ASMs (which include the most used ASMs in Australia) as the first monotherapy for an individual patient. This ability is illustrated in 100 randomly selected individuals from the pooled cohort in the online supplemental figure. Using the observed response to the prescribed ASM as the ‘ground truth’, our model outperformed five other traditional ML and deep learning algorithms in the prediction.

We have improved this model by applying natural language processing (NLP) to extract information from the text of electroencephalography (EEG) and MRI brain reports. The NLP output is incorporated as supplementary input alongside the structured clinical variables to develop a multimodality ML model. Consideration was made regarding the inclusion of sleep EEG reports, while they are not precluded from use in place of a routine EEG, for pragmatic reasons they have not been made mandatory. The improved model was reoptimised using datasets from Australian and international cohorts. Ultimately, the effectiveness of applying such a model in clinical practice would require prospective evaluation.

This article describes the protocol of a randomised controlled trial (RCT) that aims to evaluate the clinical effectiveness of the multimodality ML model in selecting the first ASM for adults with newly diagnosed epilepsy. The trial will also assess the cost-effectiveness and acceptance of the model to patients and neurologists. This protocol follows the Standard Protocol Items: Recommendations for Interventional Trials-AI extension guidelines for clinical trials of interventions involving AI.^12^

## Methods and analysis

### Study design and setting

This is a multicentre, randomised, controlled, patient and assessor blinded trial conducted in Australia. It is considered ‘first-in-class’ as the first RCT of an ML model in epilepsy management. Adults of working age with newly diagnosed epilepsy will be referred to the study by their treating clinicians. Participants will be recruited from 14 epilepsy centres across 5 Australian states from 14 February 2024 to 13 February 2026.

### Intervention

The intervention in this study is known as EpiMD, a clinical decision support software developed to assist the neurologist in selecting the first ASM. EpiMD is a multimodality ML model using the deep learning technique known as multilayer perceptron. A multilayer perceptron is focused on mapping the relationships between different variables.^13^ EpiMD includes clinical variables, as well as annotated EEG and MRI brain reports that have undergone NLP. Using these inputs, EpiMD will recommend the ASM monotherapy (from a group of seven possible choices) with which the participant is predicted to have the highest probability of achieving seizure freedom for the 12 months following ASM commencement. After consultation with the site investigators, the implementation of EpiMD will include a filter to prevent the recommendation of sodium valproate for women of childbearing age (defined in this study as between 18 and 45 years of age) owing to the medication’s teratogenic risk. No other filtering will be applied.

### Eligibility criteria

Inclusion criteria for participants are the following: aged 18–67 years, capacity to self-consent, fluent in English, diagnosis of epilepsy consistent with the International League Against Epilepsy (ILAE) definition.^14^ This is operationally defined as having had at least two seizures within the past 12 months, or one seizure within the past 6 months and epileptiform discharges on EEG, or presence of epileptogenic lesion on CT or MRI. Routine EEG and MRI brain done within 2 years prior to randomisation is also required. The routine EEG can (but is not specifically required to) be replaced with a sleep EEG.

Exclusion criteria for participants are the following: previously treated epilepsy or current ASM use for more than 14 days, pregnant or breastfeeding, current substance abuse disorder that may affect treatment adherence/response, inability to undergo EEG/MRI brain due to contraindication, presence of functional seizures, presence of progressive central nervous system disease, serious hepatic or renal disease, or terminal cancer that would affect assessment of response to ASMs.

### Recruitment procedures

Figure 1 shows the recruitment pathway. Treating neurologists will prospectively identify participants from outpatient clinics and inpatient wards using the eligibility criteria. Participants who meet the criteria will be referred to the study coordinator, who will contact the patient to explain all details of the study in addition to providing a copy of the patient information and consent form (PICF). If the participant is interested in taking part in the study, a baseline study visit in the presence of a neurologist acting as an investigator will be conducted via video link or in-person within 2 weeks of the initial referral.

**Figure 1 F1:**
[figure not shown]
Study recruitment pathway. Study recruitment pathway showing sequencing of referral, screening and consenting procedures, in addition to randomisation into the two study groups, before merging into an identical follow-up pathway. ASM, antiseizure medication; ML, machine learning; UC, usual care.

At the baseline visit, if all the eligibility criteria are fulfilled, the PICF will be signed by the participant and investigator. The baseline questionnaires will be completed by the participant, guided by the neurologist and study coordinator, to collect clinical variables alongside diagnostic test reports from the patient electronic medical record (EMR). Additionally, the content and utilisation of both the seizure diary and the healthcare use diary that will be completed at follow-up visits will be explained to the participant. Study data are collected and managed using Research Electronic Data Capture (REDCap) tool hosted and managed by Helix (Monash University).^15 16^ REDCap is a secure, web-based software platform designed to support data capture for research studies. It provides an intuitive interface for validated data capture and audit trails for tracking data manipulation and export procedures. REDCap will be used to automate the export procedures for data downloads to common statistical packages and the procedures for data integration and interoperability with external sources. The trial REDCap is updated anytime the model is utilised, and therefore, is suitable to meet our obligations regarding data management and site monitoring.

### Randomisation and ASM prescription

The participant will be randomised 1:1 into either the experimental (ML group) or the control group (usual care group) using individual randomisation centralised and in blocks that are stratified by both seizure type (focal vs generalised onset) and study site. In the experimental group, EpiMD will be run using the information provided and respond with the ASM recommendation. The investigator will prescribe the recommended ASM unless it is considered to be contraindicated due to safety reasons. In this case, the investigator will prescribe a different ASM and provide their reasoning for doing so. In the control group, the recommendation by the ML model will not be revealed, and the investigator will prescribe an ASM based only on their clinical judgement.

Any out-of-pocket costs associated with new generation ASMs used as monotherapy that are not covered by the Pharmaceutical Benefits Scheme will be reimbursed to the participants. ASM prescription will be open label for both groups. Guidance regarding the rate of titration, initial maintenance dose and any subsequent increments or decrements will be made available to the prescribing clinician. If the patient is taking an ASM prior to randomisation, the drug will be ceased over 2–4 weeks under the supervision of the treating neurologist.

### Blinding

Both the participant receiving treatment and the neurologist assessing outcomes at follow-up visits will be blinded as to which group the participant has been assigned; however, neither the patient nor the treating neurologist will be blinded to the ASM that is being taken. Blinding will be maintained through either of two methods. In method 1, the referring neurologist will act as the investigator at the baseline visit and prescribe the ASM, and different neurologist(s) will perform all subsequent follow-up. In method 2, a neurologist different from the referring one will prescribe the ASM at the baseline visit, and the referring neurologist will perform all subsequent follow-up. This allows the continuity of care at participating epilepsy clinics to be maintained.

### Follow-up procedures

Prior to a scheduled study visit, participants will be sent a REDCap survey invitation to the email they have provided. This email includes a link to a series of surveys associated with the upcoming visit as listed in table 1. These will be limited to only the seizure diary and the Liverpool Adverse Events Profile (LAEP) for the minor follow-up visits (8 weeks, 16 weeks and 40 weeks). For the major visits (28 weeks and 52 weeks), the patient will also complete surveys on mood, quality of life, healthcare utilisation and productivity. During the follow-up visits, the surveys will be reviewed for completion and discussed with the participant. If assistance is required, the participants can opt to complete the surveys together with the neurologist and the study coordinator during follow-up visits.

**Table 1 T1:** Schedule of assessments

Questionnaire	Baseline	8 weeks	16 weeks	28 weeks	40 weeks	52 weeks
Informed Consent and Randomisation	X					
Demographic Information and Clinical Variable Questionnaire	X					
Seizure Diary	X	X	X	X	X	X
LAEP		X	X	X	X	X
HADS	X			X		X
EQ5D-5L	X			X		X
QOLIE-31	X			X		X
Healthcare Use Diary				X		X
WPAI-GH	X			X		X

EQ5D-5L, European Quality of Life 5 Dimensions 5 Level; HADS, Hospital Anxiety and Depression Scale; LAEP, Liverpool Adverse Events Profile; QOLIE-31, Quality of Life in Epilepsy-31; WPAI-GH, Work Productivity and Activity Impairment Questionnaire: General Health.

### Collection of saliva samples

The PICFs contain additional opt-in consent to the collection of a DNA sample for use in the current research only, future related research only, or any future research. Participants who opt in will be mailed a DNA Genotek OG-500^17^ self-administered saliva collection kit from the lead site with prepaid return postage. On return of the saliva sample, DNA extraction will be performed and the extracted DNA will be labelled according to the participants’ study number without any identifying information. The labelled DNA sample will be stored in a locked freezer at Monash University for future use.

### Participant safety and withdrawal

While this is a clinical trial involving the use of medication, the intervention in question is EpiMD rather than a new compound. Additionally, while for the ML group drug selection is guided by EpiMD, the ultimate decision lies with the neurologist. As such, the potential for an adverse reaction to the prescribed treatment beyond standard clinical care is low and is not expected to pose extra risk to participants. Adverse events will be systematically collected using the LAEP.^18^ Clinicians can enter free text to describe any adverse effects in the REDCap. The adverse reactions will be coded by standardised terminology according to the Medical Dictionary for Regulatory Activities.^19^ Participants are free to withdraw from the study at any time, for any reason, without prejudice. If a participant withdraws from the study early, their reason for early termination will be recorded in the study record.

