### Secondary outcomes

Treatment failure is defined as withdrawal of the initial ASM or the commencement of polytherapy with a second ASM, whichever is earliest.Time to first seizure after treatment initiation.Direct healthcare costs will be assessed through review of a participant managed diary at both 28 weeks and 52-week post-treatment collection.Indirect healthcare costs will be assessed as a measure of productivity loss determined from the Work Productivity and Activity Impairment–General Health questionnaire, collected at baseline, 28 weeks and 52 weeks post-treatment commencement.The incidence of depression and anxiety will be assessed through changes to HADS scores^21^ over the treatment period, which will be collected at baseline, 28 weeks and 52 weeks post-treatment commencement.Comparison of the proportion of participants who achieve a minimum increase of 12 points in the Quality of Life in Epilepsy-31 (QOLIE-31) as a measure of quality of life,^22^ supported by the general European Quality of Life-5 Dimensions-5 Level (EQ-5D-5L) survey,^23^ both of which are collected at baseline, 28 weeks and 52 weeks post-treatment commencement.To assess clinical and participant acceptance of using ML to select the first ASM, participants and neurologists involved in the trial will be invited to take part in an optional process evaluation, involving:A study-specific questionnaire developed based on the Unified Theory of Acceptance and Use of Technology 2.^24^Qualitative interviews of 25% of study patients and 25% of study neurologists.

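### The LAEP, the trial's systematic adverse-event instrument, has no baseline, so it can show symptom prevalence on treatment but not new or worsened symptoms

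*Protocol article*

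**What the plan says.** The section on participant safety and withdrawal states: "Adverse events will be systematically collected using the LAEP". It adds a second, optional source: "Clinicians can enter free text to describe any adverse effects in the REDCap". Adverse reactions are then to be coded in MedDRA terms.

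Table 1 marks the LAEP at 8, 16, 28, 40 and 52 weeks, with nothing under baseline. The text under Follow-up procedures agrees, since it brings in the LAEP only for follow-up surveys: "These will be limited to only the seizure diary and the Liverpool Adverse Events Profile (LAEP) for the minor follow-up visits" (weeks 8, 16 and 40), with further surveys added at weeks 28 and 52.

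The other rating scales are treated differently, both in Table 1 and under Secondary outcomes:
- HADS: "which will be collected at baseline, 28 weeks and 52 weeks post-treatment commencement"
- QOLIE-31 and EQ-5D-5L: "both of which are collected at baseline, 28 weeks and 52 weeks post-treatment commencement"
- WPAI-GH: "questionnaire, collected at baseline, 28 weeks and 52 weeks post-treatment commencement"

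No section describes a pre-treatment record of the LAEP items in any other form.

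**The concern.** A symptom checklist given only after treatment starts shows who has a symptom on treatment. It does not show who had it beforehand. Some participants may also arrive with symptoms caused by another drug: the eligibility criteria allow up to 14 days of antiseizure medication use at entry, and the section on randomisation and prescription has any such drug withdrawn over 2–4 weeks. Without a baseline form, the LAEP itself cannot separate those symptoms from ones that appear or worsen on the prescribed drug.

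Two things are at stake. One is how absolute LAEP frequencies can be described in the safety report. The other is the precision of any between-arm LAEP comparison, because the natural covariate, the same scale before treatment, will not exist. A statistical analysis plan could not repair either, since it cannot recover a measurement that was never taken.

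**Working it through.** The plan gives no figure on this point to reproduce. The check is a reading of the schedule, followed by a calculation of what a baseline would be worth.

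**Schedule (Table 1)**

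| Instrument | Baseline | Post-baseline visits |
|---|---|---|
| LAEP | no | 5 |
| HADS | yes | 2 |
| EQ5D-5L | yes | 2 |
| QOLIE-31 | yes | 2 |
| WPAI-GH | yes | 2 |

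The seizure diary has a baseline entry. The Healthcare Use Diary has none, but it logs resource use and is not a rating scale. Among the repeated rating scales, then, the LAEP is the most often repeated and the only one without a baseline.

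**Value of a baseline if everyone had one**

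Inputs: 117 per group and 10% dropout (Sample size section), so 117 × 0.9 ≈ 105 per arm. The baseline-to-follow-up correlation rho is not in the documents, so 0.5 to 0.7 is an assumption.

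Variance factor with baseline adjustment = 1 − rho²
- rho 0.5: 1 − 0.25 = 0.75, a 25% reduction
- rho 0.7: 1 − 0.49 = 0.51, a 49% reduction

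Detectable difference in SD units (two-sided 0.05, 80% power) = (1.960 + 0.842) × √(2/105) × √(1 − rho²)
- no baseline: 0.39
- rho 0.5: 0.33
- rho 0.7: 0.28

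At a weaker correlation of 0.3 the variance reduction is only 9% and the detectable difference 0.37 SD.

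**Value of a baseline for later enrolees only**

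Recruitment runs from 14 February 2024 to 13 February 2026 (730 days from first to last date). The article was published on 5 April 2025, which is 416 days in. With uniform accrual and the change made on that date, the share f still to be enrolled is 314/730 ≈ 0.43.

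With a missing-baseline indicator, only this share gains, so the pooled variance reduction ≈ f × rho²
- rho 0.5: 0.43 × 0.25 ≈ 11%
- rho 0.7: 0.43 × 0.49 ≈ 21%

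The detectable difference becomes 0.387 × √(1 − 0.1075) ≈ 0.37 SD or 0.387 × √(1 − 0.2107) ≈ 0.34 SD, against 0.39 SD with no baseline. A later change lowers f, and the gain falls in proportion.

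**The case against.** The strongest reply is that no planned analysis is harmed. The LAEP is neither a primary nor a secondary outcome, the Statistical analysis section names no LAEP comparison, and the Sample size section powers none. Tolerability enters the stated analyses through retention and time to treatment failure, and neither needs a baseline LAEP. HADS and QOLIE-31 have a baseline because their outcomes are defined as change, so the difference in schedule is not a contradiction. All of this stands, and it keeps the point minor.

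It also rules out several stronger readings that a reader might infer:
- **That pre-existing symptoms will be counted as adverse events and inflate the rates in both arms.** The article gives no rule that turns every endorsed item into an adverse event. Surveys are reviewed with the participant at the visit, and clinicians may describe adverse effects separately.
- **That no baseline adjustment is possible.** Only adjustment for baseline LAEP is ruled out. Baseline HADS and QOLIE-31 are collected and can serve as partial covariates.
- **That the trial loses power for a planned tolerability test.** No such LAEP test is stated.
- **That the non-randomised comparisons (sodium channel blockers against others, or recommended against non-recommended drug within the ML group) are biased on the LAEP.** The article does not say that the LAEP is among the outcomes compared.

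One further objection is fair. A baseline form would not give clean treatment-emergent rates for everyone: earlier enrolees would have none, and for participants already taking a drug at entry the baseline is not drug-free. That limits what the fix delivers and shapes how it should be reported, but it does not remove the benefit for the rest.

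**Conclusion.** The point holds as a minor gap in the design. The schedule is stated in both table and text, and it leaves the instrument named for systematic adverse-event collection without a pre-treatment value. LAEP results will therefore be on-treatment prevalence. Change and new-or-worse status cannot be derived from them, and adjustment for the scale's own baseline is ruled out.

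Randomisation balances pre-existing symptoms in expectation, so the between-arm comparison stays unbiased and the primary analysis is untouched. The effect is on safety and tolerability reporting and on precision.

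The realistic gain in precision is about 11% to 21% of variance. This assumes a correlation of 0.5 to 0.7, uniform accrual and a change made at publication. The 25% to 49% figure would need a baseline from every participant. Either figure shrinks if baseline HADS or QOLIE-31 is already used as a covariate.

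**What to change.** 1. Add the LAEP to the baseline column of Table 1 for all participants still to be enrolled, completed with the other baseline questionnaires and before the prescribed drug is started.
2. Adjust any between-arm LAEP comparison for the baseline score, with a missing-baseline indicator so that earlier enrolees stay in the analysis.
3. Report new-or-worse symptoms only for participants with a baseline, noting any antiseizure medication being taken at entry.
4. For everyone else, describe LAEP results as on-treatment prevalence. This step is useful even if recruitment has closed.

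The cost is a minor amendment and a few minutes of participant time at a visit where questionnaires are already completed. The downside is that baseline data will be partial, so new-or-worse results will cover only later enrolees.
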